### **4.2 Secondary objectives**

- 4.2.1 Main secondary

- Intensive assessment of a nested subset of **about 1,000** patients to evaluate the effect of the administration of Eurartesim® on blood biochemistry, full blood count and QTc intervals.
- QTc interval and piperazine concentration relationship will also be investigated in all the **nested 1,000** patients.

- 4.2.2 Other secondaries

- Description of the prevalence of *Plasmodia* species (*falciparum*, *vivax*, *ovale*, *malariae*) as confirmed by blood smear results in the nested subset of 1,000 patients and retrospective comparison of the tolerability profiles between the two sub-populations of patients infected with *Plasmodium falciparum* and patients infected with other *Plasmodia*.
- Assessment of the relationship between the occurrence of adverse events and the administration of concomitant medications will be made in the subset of 1,000 patients.

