### 3.3 Malaria in Burkina Faso, Mozambique, Ghana and Tanzania

#### Ghana

Malaria is the leading cause of morbidity and mortality reported in health facilities in the Northern areas where Navrongo HDSS is located. **Malaria transmission occurs during most months of the year but there is a distinct seasonal pattern with the peak of**

transmission coinciding with the period of the major rains (May – October) and the dry season (November – April) seeing very low rates of malaria infection. Transmission has been estimated to be 418 infective bites per person per year. The main malaria vectors are *A. gambiaes.l* and *A. funestus* constituting about 94.3% of the vector population. The predominant parasite species is *P. falciparum* (accounting for more than 90% of all infections). *P. malariae* is seen in a small proportion of infections (less than 5%) and some mixed infections of *P. falciparum* and *P. malariae*. *P. ovale* is rarely seen and no *vivax* is seen. The incidence of clinical malaria also shows some seasonality with an incidence density of infection varying from five cases per person- year in the dry season to over seven cases per person-year in the wet season. In a just concluded study of malaria morbidity and mortality in a birth cohort of children in the district (n=2200), 38.9% of all admissions in this cohort was due to malaria with malaria accounting for 50.9% of all hospital visits made by cohort members (unpublished data).

In the middle belt of Ghana where the Kintampo HDSS is located, The parasite prevalence in children <10 years of age is >50% all year round and the incidence of clinical malaria among children less than 5 years is about 7 episodes per child per year. The main vectors for transmission of malaria are *Anopheles gambiae* and *A. funestus* and the transmission is perennial but peaks between April and October. The annual entomological inoculation rate was 269 infective bites per person per year in 2005. Malaria is diagnosed by clinical suspicion and confirmed with rapid diagnostic test or microscopy. The first line treatment for malaria is artesunate-amodiaquine or arthemether-lumefantrine for uncomplicated malaria and quinine for complicated malaria. Chemical shops are the first point of call during a child's febrile illness and use of traditional medicine and left over drugs at home is also common in the study area.

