#### **7.4 Thick blood smear logistics**

All thick blood smear slides will be stained and stored for independent confirmation of presence or absence of malaria parasites. They will be examined in the laboratory by qualified personnel and according to the laboratory's Standard Operating Procedures. The results will be transferred for data entry in the form of listings. The blood slides will be performed on Day 1 for all the participants..

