#### **Additional analysis in the sub-set population**

QTc data will be recorded and centrally analysed according to the method described in the ICH guideline E14. The impact of all recorded covariates on QTc prolongation will be investigated through analysis of covariance techniques.

For the AESIs possibly related to cardio-toxicity, a correlation analysis with QTc values recorded at the visit of Day 3 (both before and 3-4 hour after treatment administration) will be carried-out. Occurrence of these events will also be studied with respect to distance from food intake.

Laboratory values will be analysed after normalization. Shift tables from normal to abnormal and vice-versa will be generated.

All the analyses previously described will be also performed by class of age and by type of Plasmodium.

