### **9.3 Determination of sample size**

According to the cases registered in the previous years in the area where the study is performed, it should be possible to include approximately 10,000 cases of malaria confirmed by a parasitological diagnosis or diagnosed according to WHO criteria. This number of cases will allow identification of “rare” adverse events (incidence: 1 case/3,000 patients) with a 95% probability.

The sample size computation for the nested study (~1,000 patients) has been also based on feasibility considerations. The focus of this sub-set study will be on the combination of AESIs related to cardio-toxicity/prolonged QT (see above). In this sub-set, there will be a probability of 0.95 (0.865) of observing at least one cardiac AESI assuming that the true incidence of this event is 0.003 (0.002). For such a sample size, if no events have been observed, the upper limit of the 95% confidence interval for the probability of such event is 0.003.

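### The falciparum versus other-species comparison is confined to the nested 1,000 although Day 1 smears are read for everyone; the co-medication objective has a similar but milder scope problem

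*Protocol*

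**What the plan says.** **Species.** Section 4.2 sets the comparison of falciparum with other Plasmodia "in the nested subset of 1,000 patients and retrospective comparison of the tolerability profiles between the two sub-populations". The synopsis (Objectives) and section 5.4 place it there too. Section 9.2 ends by asking for all analyses by type of Plasmodium, but that sentence stands under the sub-set heading, so its reach is unclear.

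**Smears.** Section 7.4: "The blood slides will be performed on Day 1 for all the participants". The slides are examined in the laboratory and the results sent for data entry. Section 8.2 uses the initial parasite species in the review of AE charts, with no limit to the subset.

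**Species mix.** Section 3.3 describes P. falciparum in northern Ghana as "accounting for more than 90% of all infections", and gives 99% for the Nouna area in Burkina Faso.

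**Co-medication.** Section 4.2 says that the assessment of AEs against "administration of concomitant medications will be made in the subset of 1,000 patients". The synopsis and section 5.4 agree. The first part of section 9.2, headed as covering both the whole sample and the subset, plans to relate AESIs to previous and concomitant drugs. Medication is recorded for all patients at Day 1, at the Day 5 contact and at unforeseen visits (whole-sample flow chart, sections 7.2.2 and 7.2.3).

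**Food.** Under the sub-set heading of section 9.2, on cardiac AESIs: "Occurrence of these events will also be studied with respect to distance from food intake".

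**The concern.** A comparison between species is limited by the smaller group. If nearly all patients have P. falciparum, 1,000 patients leave few others, while smears from the remaining 9,000 are read and then not used for this question. The likely result is an interval so wide that a real difference in tolerability could not be told from none.

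For co-medication, the protocol sets two scopes for closely related questions (all AEs in the subset, AESIs in everyone) and gives no reason. Rare AEs other than AESIs, where more patients would help most, are left in the smaller cohort.

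**Working it through.** **1. The protocol's own figures.** Section 9.3 states that in the subset "there will be a probability of 0.95 (0.865) of observing at least one cardiac AESI" at true incidences of 0.003 (0.002). With P = 1 − (1 − p)^n and n = 1,000, this gives 0.950 and 0.865, as stated. For n = 10,000 and p = 1/3,000 it gives 0.964 against the stated 0.95 (0.950 is reached with 9,000). These figures concern seeing at least one event. The protocol gives no precision for the comparisons discussed here.

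**2. Species: precision.** Inputs:
- Non-falciparum share of 1% to 10%, from the two sites in section 3.3. Above 90% falciparum means that 10% is an upper bound there. The range is assumed for the other sites.
- AE risk p = 0.10 in both groups (assumption).
- If half of the 9,000 main-group slides are positive (assumption), N = 4,500 + 1,000 = 5,500.

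Half-width = 1.96 × √[p(1 − p)(1/n₁ + 1/n₂)].

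| Non-falciparum share | N = 1,000 | N = 5,500 | N = 10,000 |
|---|---|---|---|
| 1% | 10 v 990: ±18.7 | 55 v 5,445: ±8.0 | 100 v 9,900: ±5.9 |
| 5% | 50 v 950: ±8.5 | 275 v 5,225: ±3.6 | 500 v 9,500: ±2.7 |
| 10% | 100 v 900: ±6.2 | 550 v 4,950: ±2.6 | 1,000 v 9,000: ±2.0 |

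(percentage points)

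Example: 1.96 × √[0.09 × (1/10 + 1/990)] = 1.96 × 0.0953 = 0.187. At a fixed share the half-width scales with 1/√N, so N = 5,500 is √(10,000/5,500) = 1.35 times as wide as N = 10,000.

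**3. Species: power and exact check.** The normal approximation is rough with one expected event among 10 patients. Power to detect a doubling from 10% to 20% (two-sided 0.05), at shares of 1%, 5% and 10%:
- N = 1,000: 0.25, 0.59 and 0.80 (exact Fisher test: 0.13, 0.52 and 0.78).
- N = 10,000: 0.85, above 0.99 and above 0.99.

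For an AE never seen in the non-falciparum group, the exact two-sided upper limit is 1 − 0.025^(1/n): 31% for n = 10, 7.1% for n = 50 and 3.6% for n = 100.

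**4. Co-medication.** With 10% to 50% of patients exposed (assumption):
- 10% AE rate doubled: power 0.80 to 0.99 in 1,000 patients, above 0.99 in 10,000.
- 0.3% AE rate doubled: power 0.11 to 0.14 in 1,000, 0.38 to 0.61 in 10,000.

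**5. Food interval.** Expected cardiac AESIs in the subset are 1,000 × 0.002 = 2 to 1,000 × 0.003 = 3. If patients split evenly by food interval (assumption), the smallest possible two-sided Fisher p is 0.50 with 2 events and 0.25 with 3. At least 6 events are needed for p < 0.05.

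**The case against.** The subset is the better-observed cohort. It has microscopic confirmation before treatment and AEs solicited on Days 3 and 7. The main group includes clinically diagnosed patients and has one scheduled contact, possibly by telephone. Section 9.2 calls the analysis mainly descriptive, no power is claimed, and the synopsis itself expects the vast majority to have P. falciparum. All of this stands as a reason to keep the nested result and to stratify by cohort. It does not justify setting aside the other smear-positive patients, since a species contrast within each cohort compares patients followed in the same way.

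Two limits on the gain also stand. The tenfold increase is an upper bound, because some main-group slides will be negative. And section 7.4 describes slide reading as presence or absence of parasites, although section 8.2 presumes that species is known.

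A reader might infer more than the protocol supports:
- **That co-medication is wholly confined to the subset or unanswerable there.** Section 9.2 covers AESIs in the whole sample, and step 4 shows adequate power for common AEs.
- **That drugs given to treat an AE would count as exposures.** The protocol is silent on this, and an exposure window is ordinary content for the statistical analysis plan.
- **That the food analysis should move to all 10,000.** It is an analysis in section 9.2, not an objective in section 4.2. The Day 1 to Day 3 food questionnaire (section 7.1) exists only in the subset. Elsewhere food timing is recorded at dose 1 and when a cardiac AESI is suspected, so a move would need new data resting on recall. Nor can 20 to 30 cardiac AESIs be assumed in the whole sample: section 9.3 gives its incidence for the subset, and main-group patients have no scheduled ECGs.

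**Conclusion.** The point holds for species. Restricting the comparison to the subset leaves 10 to 100 non-falciparum patients and an interval of ±18.7 to ±6.2 points. Using all smear-positive patients would bring this to about ±8.0 to ±2.6 (half of main-group slides positive) or at best ±5.9 to ±2.0. The sizes rest on a 10% AE risk and on a species mix taken from two sites. The subset is very weak at a 1% share and only modest, not empty, at 10%.

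For co-medication the defect is an unexplained difference in scope between section 4.2 and section 9.2, and it costs power mainly for rare AEs. The food-interval analysis is correctly placed, but 2 to 3 expected events allow description only. The primary objective is unaffected.

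**What to change.** - Reconcile the synopsis (Objectives, Evaluation criteria), section 4.2 and section 5.4 with section 9.2, and state which analyses the closing sentence on type of Plasmodium covers.
- Run the species comparison in all patients with a positive Day 1 smear, and the all-AE by co-medication analysis in all treated patients. Stratify both by cohort (main or nested) and HDSS site. Report the nested-subset result as a supporting analysis.
- State that species is entered in the slide listings for main-group patients as well.
- Keep the food-interval analysis of cardiac AESIs in the subset and label it descriptive.

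The cost is mainly wording. No new samples or patient contacts are needed. If main-group slides are currently read only for presence or absence, recording species adds reading work. The statistical downside is less intensive AE capture in the main group, which the cohort stratum handles.

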## 5. DESCRIPTION OF THE STUDY

### 5.1 Description of the study design

This is an observational, non-comparative, longitudinal study, conducted on approximately 10,000 patients with signs and symptoms of uncomplicated malaria suspected or confirmed by a parasitological diagnosis or, when this test is not available, by WHO diagnostic criteria.

A subset of **about 1,000** patients will be assessed more closely for QT interval prolongation and laboratory tests. In this subset, the presence of *Plasmodia* of any species will be confirmed by microscopy. **Plasma samples from all the 1000 patients will also be taken for evaluation of** PQ concentration at different timepoints. From such blood drawings and before centrifugation, three drops of whole blood will be spotted on filter papers. These filter papers will be utilized to determine whole blood piperazine concentration with the Dry Blood Spot methodology (if a validated analytical method for such determination will be settled up at the time of the study course).

The study will take place in several public health facilities in up to **7** HDSS centres (Health and Demographic Surveillance Sites) in Burkina Faso (**2**), Mozambique (1), Ghana (3), and Tanzania (1), where Eurartesim® will be used as first-line treatment of uncomplicated malaria episodes. The patients will be admitted to the entry visit following the usual procedures of the HDSS centre. The subset of **about 1,000** patients will be constituted by patients who agree to participate in the closer monitoring conditions.

In case of treatment inefficacy or safety concerns, medicines recommended by the NMCPs of each country will be prescribed as rescue treatments.

All patients visiting one of the health facilities referring to the HDSS centres and for whom a diagnosis of uncomplicated malaria (according to the WHO criteria) is suspected or confirmed by a parasitological diagnosis will be enrolled in the study after their informed consent (a parent's or guardian's consent form **signature will be required for children as per each country regulation**) has been obtained. For teenagers (age depending on country regulations), an assent to participate in the study will be also sought if required by the National guidelines. A thick blood smear will be prepared for microscopic diagnosis. **For the participants consented into the main group, eurartesim® tablets will be prescribed to the patients (or to the parents/guardians if the patients are children) meeting the protocol inclusion criteria before the results of the thick blood smear are known if malaria has already been confirmed from RDT and/or clinical examination as per country regulations.**

The patients will be contacted at Day 5 ( $\pm$  2 days) by a community health agent (CHA) of the HDSS, in order to capture recovery status and all the experienced adverse events. A visit by the community health agent will be scheduled on all the cases in which the information collected during the telephone contact should be considered incomplete or unreliable ones. Special procedures will be followed in case of serious and/or severe adverse events and events classified of special interest (see specific section).

The subset of 1,000 patients will be intensively followed-up. These patients will have haematology (Hb and full blood counts (RBC, WBC and WBC differential count)) and standard biochemistry (BUN, Creat, ALT/AST, Bilirubine, electrolytes (K+ and Cl)) undertaken at Day 1 (before drug administration), Day 3 (3-4 hours after the last dose of treatment), and Day 7.

**Each blood sampling for both haematology and biochemistry requires about 2mL of venous whole blood. This makes up for a total amount of about 6mL of venous whole blood to be taken from each participant in the nested group for the entire study period.**

If the results are abnormal, the blood examination will be repeated until normalization. Triplicate ECG and blood sampling for PQ concentration assessments (in all the 1,000 patient subgroup) will be performed on Day 1 (before drug administration); single ECG and blood sampling for PQ concentration (in all the 1,000 patient subgroup) will be repeated on Day 3, before the last dose of Eurartesim® and 3 to 4 hours after the last drug administration (in this latter case ECG will be performed in triplicate), as well as on Day 7; safety information will be collected at all these visits. **Each PK sample will be 2 mL of whole blood which makes a total of 8 mls for the entire study period unless clinically indicated.**

If the QTcF (QT corrected by Fridericia's formula) value assessed on Day 3 before last dose is above 500 ms, Eurartesim® should be withheld until QTcF returns below 480 ms within 6 hours. Thereafter, the Eurartesim® cycle may be completed under frequent QTc monitoring based on medical judgment. If the QTcF should not return below 480 ms within 6 hours, another antimalarial therapy should be considered.

The occurrence of any adverse events will be solicited from the subset of **about 1,000** patients on Days 3 and 7 following administration of Eurartesim® as well as in any additional visits.

All patients in the study with a cardiac event of special interest (see section 8.5) will have an ECG performed.

Patients will be asked to report to the health facility or to the HDSS if any adverse event occurs after Day 5 ( $\pm$  2 days) contact and within 28 days after the start of Eurartesim® intake.

Female patients will be encouraged to communicate to the study team if they get pregnant within a period of two months after the start of the Eurartesim® treatment. In these cases, information on the evolution of the pregnancy will be collected at 3, 6, 9 months and after the delivery (6 and 14 weeks). Information on the drugs taken during the pregnancy as well as AEs/SAEs/AESIs and the health status of the newborn/s will be collected.

## 5.2 Study duration

The study will last approximately two years.

## 5.3 Drug prescription and dosing

The patients will be instructed to take Eurartesim® (DHA/PQP) with a dose regimen of one administration every 24 hours over a period of three days, i.e. at Day 1, then after 24 hours (Day 2) and after 48 hours (Day 3) from the first administration.

The dose will be based on body weight **as depicted in the table below**. Two strengths of Eurartesim® will be provided to facilitate the dosing in children and adults: 20/160mg and 40/320mg of DHA and PQP respectively.

| Body weight (kg) | Daily dose (mg)                                          | Number of tablets per dose |                  |
|------------------|----------------------------------------------------------|----------------------------|------------------|
|                  |                                                          | 20/160mg DHA/PQ            | 40/320mg DHA/PQ  |
| 5 to <7          | 10 mg DHA and 80 mg PQP                                  | ½ tablet            |                  |
| 7 to <13         | 20 mg DHA and 160 mg PQP                                 | 1 tablet            |                  |
| 13 to <24        | 40 mg DHA and 320 mg PQP                                 |                            | 1 tablet  |
| 24 to <36        | 80 mg DHA and 640 mg PQP                                 |                            | 2 tablets |
| 36 to <75        | 120 mg DHA and 960 mg PQP                                |                            | 3 tablets |
| 75 to <100       | 160 mg DHA and 1280 mg PQP                               |                            | 4 tablets |
| > 100            | There are no data on which to base a dose recommendation |                            |                  |

The patients will be instructed to take Eurartesim® with water, at least three hours before or three hours after food intake (i.e. three hours after the previous food intake with no food intake for the following three hours after Eurartesim® administration).

To facilitate drug administration in small children, tablets will be crushed on a spoon and given with water. If vomiting occurs within 30 min from drug administration, dose will be re-administered. If vomiting occurs within 30 to 60 min, half a dose have to be re-administered. Re-dosing should not be attempted more than once. The first study drug administration will be supervised at the site in all the patients, instruction on the second and the third drug administration will be given to patients.

In the nested 1000 patient group, the second administration will be given preferably at the study site or at the patient's home by a trained CHA. If the dose is administered at home, a specific diary will be provided to the patient in which the CHA have to fill in the second drug administration data. This diary will be maintained by the patient and will be returned to the site when the third administration will be provided (at the site).

Eurartesim® will be provided free of charge by Sigma-Tau ifr S.p.A.

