| Population
Selection criteria | 
Inclusion Criteria
 
 
• Uncomplicated malaria (Plasmodia of any species) diagnosed as per national policies and in line with WHO recommendations (a history of fever in the previous 24 h and/or the presence of anaemia, for which pallor of the palms appears to be the most reliable sign in young children). Confirmation of malaria by a parasitological diagnosis (Microscopy/RDT) is encouraged but its absence does not prevent patients from being enrolled.
 
• Age <math>\geq</math> 6 months and weight <math>\geq</math> 5 kg.
 
• Capability of taking an oral medication.
 
• Ability and willingness to participate based on signed informed consent (a parent or a guardian has to sign for children below 18 years old), or on verbal consent given in front of a witness signing the informed consent, and access to health facility. The patient has to comply with all scheduled follow-up visits.
 
 
Exclusion Criteria
 
 
• Known allergy to artemisinin or to piperaquine.
 
• Known pregnancy.
 
• Lactating women should be excluded if other anti-malarial treatments are available
 
 |

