### 6.2 Selection criteria

#### 6.2.1 Inclusion criteria

- Uncomplicated malaria (*Plasmodia* of any species) diagnosed as per national policies and in line with WHO recommendations (a history of fever in the previous 24 h and/or the presence of anaemia, for which pallor of the palms appears to be the most reliable sign in young children). Confirmation of malaria by a parasitological diagnosis with RDT is encouraged but its absence does not prevent patients from being enrolled.
- Age  $\geq 6$  months and weight  $\geq 5$  kg.
- Capability of taking an oral medication.
- Ability and willingness to participate based on signed informed consent (a parent or a guardian has to sign for children below 18 years old), or on verbal consent given in front of a witness signing the informed consent, and access to health facility. The patient is to comply with all scheduled follow-up visits.

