#### 6.3.2 Patient selection

At least 10,000 **treated** malaria cases will be enrolled. A subset of about 1,000 patients will be assessed more closely. Each patient will be included once.

A patient will be included in the study in case he/she meets the selection criteria of the protocol and agrees to participate. In particular, in order to enter the study, the patient should accept that one drop of blood is taken for the preparation of a thick blood smear, that the community health agent contact him/her at home, that the data collected during those visits are registered and analyzed and finally that, in case of an SAE and/or an AE classified as severe and/or an AESI (see section 8.5) should occur he/she has to contact immediately the community health agent or the HDSS, directly.

The subset of **about 1,000** patients will need to accept to be strictly monitored at the health facility or HDSS, where a capillary blood sample is taken in order to prepare a thick blood smear, a venous blood sample is collected for chemistry, full blood count and PQ concentration assessment (in all the 1000 patient subgroup), and a triplicate ECG recording is performed before the start of the treatment. Furthermore, he/she has to agree to be visited again on day 3 and day 7 after start of the treatment, to run all the evaluations foreseen by the study protocol.

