### 7.2 Collected data

#### 7.2.1 Registry at the HDSS centre

Each patient visiting one of the designated study health facilities within the HDSS, suspected to have uncomplicated or complicated malaria, regardless of him/her being included in the study, will be recorded in a specific registry by the study team member who has examined him/her. The date of consultation, the age and sex of the patient, the village or neighbourhood he/she lives in, the recent history of any anti-malarial treatment intake, the weight, the clinical signs, the diagnosis, the prescribed treatment (dose and duration) will be reported in this document as well as the patient ID number (if recruited in the study) or the possible reason for not participating in the study. In this registry, for the patients included in the study, will be also reported the date on which the patient's chart was provided to the CHA (by the

HF) as well as the date in which the CHA consigned the filled in chart with data referring the follow-up contact at Day 5 ( $\pm 2$  days) at the HF; those dates will be reported for traceability purposes.

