### **7.3 Patients who did not receive follow-up visits/contacts**

#### **7.3.1 Premature discontinuation before drug intake**

**In case a participant fulfils all selection criteria, he/she is enrolled in the study and is attributed an enrolment number/participant ID number. If for any reason, the participant cannot be given the study drug and must discontinue participation in the study, the reasons for this will be collected by the CHA or HF staff.**

**These particular subjects will not be part of the safety and efficacy analysis. Additional subjects will need to be recruited in the study in order to make up for the total of 10,000 (9,000 and 1,000) subjects needed for analysis.**

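### Patients of 100 kg or more meet the selection criteria, but the protocol has no dose for them

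*Protocol*

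**What the plan says.** Protocol section 6.2.1 requires "Age $\geq 6$ months and weight $\geq 5$ kg", and the summary repeats the criterion. Neither place gives an upper weight limit, and neither exclusion list (summary, section 6.2.2) refers to weight.

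Section 6.3.2 turns these criteria into the rule for entry: "A patient will be included in the study in case he/she meets the selection criteria of the protocol and agrees to participate". Section 5.1 adds that, in the main group, tablets are prescribed to patients who meet the inclusion criteria.

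Section 5.3 bases the dose on a body-weight table, and section 7.2.2 confirms that weight determines the dose. The highest dosed band runs from 75 kg to below 100 kg (160 mg DHA and 1280 mg PQP, four tablets). The last row covers weights above 100 kg and contains only the statement "There are no data on which to base a dose recommendation".

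Section 7.3.1 has a general fallback for someone already enrolled: "If for any reason, the participant cannot be given the study drug and must discontinue participation in the study". The reasons are collected, the person is left out of the analysis, and another is recruited.

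**The concern.** Eligibility and dosing should cover the same weights. They agree at the bottom, where both start at 5 kg, but not at the top. A patient of 100 kg or more satisfies every selection criterion, yet staff have no protocol dose to give.

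Two things are at stake:

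- **Avoidable burden.** Such a patient can be consented and enrolled and, in the nested subset, bled and given ECGs before anyone establishes that there is no dose.
- **Unclear handling of a QT-prolonging drug.** A statement that data are lacking does not instruct staff to withhold treatment, and at exactly 100 kg the table says nothing. Facilities across up to seven surveillance sites could act differently. If one of them extrapolated a dose, that patient would be treated and so fall outside section 7.3.1. The compliance ratio in section 9.2 would then lack a defined denominator, because it divides tablets taken by tablets that should have been taken.

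**Working it through.** The protocol states no figure on this point, so the check compares the eligible weight range with the dosing table.

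**Inputs**

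- Eligible range (summary and section 6.2.1): 5 kg and above, no upper bound.
- Dosed bands (section 5.3), each including its lower end and excluding its upper end: 5 to 7, 7 to 13, 13 to 24, 24 to 36, 36 to 75 and 75 to 100 kg.
- No-dose row (section 5.3): strictly above 100 kg.

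**Coverage**

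| Weight (kg) | Eligible? | Daily PQP dose from the table |
|---|---|---|
| 4.9 | No | none |
| 5 | Yes | 80 mg |
| 7 | Yes | 160 mg |
| 13 | Yes | 320 mg |
| 24 | Yes | 640 mg |
| 36 | Yes | 960 mg |
| 75 | Yes | 1280 mg |
| 99.9 | Yes | 1280 mg |
| 100 | Yes | no row |
| 100.1 | Yes | row without a dose |
| 120 | Yes | row without a dose |

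Every weight from 5 kg to just below 100 kg has exactly one dose. The uncovered part of the eligible range is 100 kg and above.

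**Day 1 burden for an affected nested-subset patient, before dosing**

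- Haematology and biochemistry: 2 mL (section 5.1: "Each blood sampling for both haematology and biochemistry requires about 2mL of venous whole blood").
- Piperaquine sample: 2 mL (section 5.1: "Each PK sample will be 2 mL of whole blood").
- Total: 2 + 2 = about 4 mL of venous blood.
- ECG: one triplicate recording, that is, 3 tracings.

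**Coverage after the fix**

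- With an upper limit of less than 100 kg, the eligible range is 5 kg to below 100 kg, and the six dosed bands cover it without gap or overlap.
- Changing only the last row to start at 100 kg closes the gap at that single value but leaves patients of 100 kg or more eligible without a dose. The eligibility change is the essential part.

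**Dose per kilogram if the top band were instead closed at 100 kg**

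- At 100 kg: 1280 / 100 = 12.8 mg/kg PQP.
- Limit approached at the top of the 36 to 75 kg band: 960 / 75 = 12.8 mg/kg.
- Lowest limit in the table, at the top of the 5 to 7 kg band: 80 / 7 = 11.4 mg/kg.

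Four tablets at exactly 100 kg would therefore stay within the mg/kg range the table already allows.

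**The case against.** The case for leaving the text alone is reasonable. The protocol does address heavy patients: section 5.3 has a row telling staff that no dose can be recommended, and the first dose is supervised at the site for everyone. Section 7.3.1 then deals with anyone enrolled who cannot be treated. Weight is recorded for every suspected case, so a heavy patient would probably be noticed. The burden arises only if staff overlook the table until after the blood draws and ECGs. At exactly 100 kg the four-tablet band is closed by its own inequality, so the literal reading is that no dose applies. An amendment in four countries also takes real effort.

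Much of this stands. The effect on the estimates is negligible, the number of patients is unknown and probably small, and the gap at exactly 100 kg concerns a single value. It does not remove the mismatch. Section 7.3.1 acts only after enrolment, and only if staff conclude that the drug cannot be given. The table reports missing data and does not prohibit dosing. The protocol also does not say whether weighing comes before consent. The objection supports a low priority, not dropping the point.

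**Conclusion.** The concern holds. For weights of 100 kg and above, the selection criteria admit patients for whom section 5.3 provides no dose, and exactly 100 kg has no row at all.

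The size is minor. No sample-size statement changes, and the effect on the incidence estimates is negligible provided section 7.3.1 is applied as written. For an affected nested-subset patient, the cost is up to about 4 mL of venous blood and three ECG tracings before dosing. The protocol gives no weight distribution, so no patient count can be stated. That few would be affected is an assumption.

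**What to change.** Add weight below 100 kg to the inclusion criteria in the summary and section 6.2.1, and change the last row of the section 5.3 table so that it starts at 100 kg.

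If the clinical team prefers, the top band can be extended to include 100 kg and patients above 100 kg excluded. That is a clinical decision.

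The text change is one line in two places and one symbol in the table. It needs a written amendment under section 12, signed by the Principal Investigators and the Sponsor and possibly submitted to ethics committees, so it is sensible to combine it with another amendment. No new measurement is needed, because the section 7.2.1 registry already covers all suspected cases, included or not: "the weight, the clinical signs, the diagnosis, the prescribed treatment (dose and duration) will be reported in this document". The downside is that a few heavy patients would not be enrolled and would presumably receive the antimalarial recommended by their national programme.
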